### Recruitment {15}

We assume that cooperation agreements will have to be concluded with several companies and hospitals to achieve the planned number of cases. It is planned to conduct three survey waves, each lasting 6 months (3 months of intervention followed by 3 months of exchange in the waiting-control design). As a result, a recruitment period totalling 18 months is planned.

Before the cooperation agreements are finalized, site visits will be conducted at the companies and hospitals. During the first contact between employees of the participating companies and the trial staff, information will be provided regarding the purpose and procedures of the trial. At this stage, employees will receive written information as well as detailed informed consent. After an appropriate period for consideration, participants will have the opportunity to ask questions, verification of inclusion and exclusion criteria will be conducted, and written consent will be obtained. Following this, participants will be enrolled in the trial, and the scheduling of the baseline assessment will occur.

## Assignment of interventions: allocation

### Sequence generation {16a}

Using a randomization software (https://www.randomizer.at), participants will be randomized in a 1:1:1 allocation ratio to three study arms: control, passive back-support exoskeleton model 1, and passive back-support exoskeleton model 2. Randomization will be stratified by sector (logistics or healthcare), trial site (participating cooperation partners), and sex (women or men) to ensure balanced group allocation across occupational contexts. Permuted block randomization with a block size of 6 will be used.

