### Sample size {14}

This study is designed as a feasibility-oriented randomized controlled trial with a primary focus on intervention adherence under real-world working conditions. Primary feasibility outcomes include the following: (1) *task-level compliance with exoskeleton use* (worn for at least 50% of the time during lifting tasks) and (2)* study-level adherence* (defined as at least 75% retention through the 3-month assessment). The sample size is therefore primarily determined by feasibility considerations, including the availability of exoskeleton devices, recruitment capacity within cooperating companies, and the fixed project timeline.

Due to the lack of comparable prospective long-term studies on passive back-support exoskeletons in occupational settings, a formal a priori sample size calculation based on expected effect sizes for musculoskeletal outcomes was not feasible. Consequently, the study is not powered to provide confirmatory evidence regarding effectiveness-related outcomes.

Participants will be randomized using a 2:1 allocation ratio (intervention to control). The recruitment target is defined in terms of evaluable participants: 80 complete datasets in the intervention group and 40 complete datasets in the control group (total *n* = 120 complete datasets). A complete dataset is defined as outcome data available at baseline, at two intermediate follow-up assessments after 1 and 2 months, and at the final assessment after 3 months.

Given the real-world occupational setting and the multi-visit follow-up schedule, substantial attrition is anticipated. Assuming a conservative dropout rate of up to 50%, achieving 120 complete datasets may require randomizing up to approximately *N* = 240 participants (≈160 intervention, ≈80 control). Recruitment will therefore continue until these complete-dataset targets are reached, or until a maximum of *N* = 240 participants have been randomized, whichever occurs first, subject to feasibility constraints (e.g., device availability, company participation, and project timeline). The recruitment stopping rule is based on follow-up completeness and feasibility considerations and is not linked to interim effectiveness results.

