### Concealment mechanism {16b}

Allocation concealment will be ensured through centralized computer-based randomization. Group assignment is generated by the randomization software only after a participant has been enrolled and baseline eligibility has been confirmed. Investigators involved in recruitment and enrollment will not have access to the upcoming allocation sequence.

Due to the visible and physical nature of the intervention (use of a back-support exoskeleton), blinding of participants and intervention personnel is not feasible.

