### Implementation {16c}

The random allocation sequence is generated by a member of the study team who is not involved in participant enrollment or data collection.

Participants are enrolled by trained research staff at the respective study sites.

Group assignment is conducted automatically by the randomization software after enrollment, ensuring allocation concealment.

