## Assignment of interventions: blinding

### Who will be blinded {17a}

This study is designed as an open-label randomized controlled trial, as blinding of participants and staff delivering the intervention is not feasible due to the visible and physical nature of the exoskeleton. Consequently, neither participants nor those overseeing the intervention will be blinded. However, to mitigate potential bias, outcome assessors and data analysts will remain blinded to group assignment, and all data will be pseudonymized prior to analysis to ensure objectivity. We acknowledge the risk of performance bias and detection bias, particularly in subjective outcome measures such as perceived workload, fatigue, or job satisfaction. To address these risks, we use validated and standardized questionnaires to reduce the influence of personal interpretation. Furthermore, participants in both arms will receive comparable levels of researcher attention and contact, helping to minimize differential expectations or behavior changes that could otherwise influence the results.

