## Statistical methods

### Statistical methods for primary and secondary outcomes {20a}

Data will be analyzed using IBM SPSS Statistics (Version 29; IBM, Armonk, New York, USA). For the primary effectiveness analysis, both exoskeleton arms (Exo1 and Exo2) will be pooled into a single intervention group and compared to the control group. Exploratory analyses will additionally compare the three randomized arms separately. The primary analysis will follow an intention-to-treat (ITT) approach, meaning that all randomized participants will be analyzed in the groups to which they were initially assigned. Data from participants with missing information will be analyzed under the "missing at random" assumption. Per-protocol analyses will include only those participants in the intervention group who wore the exoskeleton at least 75% of the days each week when lifting tasks are performed. These analyses will be conducted as sensitivity analyses to assess the robustness of effectiveness-related estimates with respect to intervention adherence and wearing behavior. 

The primary applicability endpoint will be assessed descriptively. To evaluate the metric endpoints, mixed-effects models with a repeated measures structure will be estimated using restricted maximum likelihood. In this model, the measured values collected during all study visits will be considered the dependent variable. We will include treatment group (exoskeleton vs. control) and categorical time as fixed effects. Interactions between the group and time (categorical) will also be modeled. For random effects, we will include an intercept for each subject. Within the mixed models, we will estimate 95% confidence intervals (CIs) and *p*-values for contrasts between groups for the 3-month period. For sensitivity analyses, only patients with complete paired baseline and 3-month follow-up data will be included, ensuring a time difference within groups is analyzed using a paired *t*-test for dependent samples.

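### One fixed, published block size of 6 within company-by-sex strata of an open-label trial could let a recruiter who tracks allocations predict up to 29% of exoskeleton-versus-control assignments with certainty

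*Protocol article*

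**What the plan says.** The section on sequence generation {16a} sets the ratio ("participants will be randomized in a 1:1:1 allocation ratio to three study arms") and the block structure ("Permuted block randomization with a block size of 6 will be used"). It also sets the strata: "Randomization will be stratified by sector (logistics or healthcare), trial site (participating cooperation partners), and sex (women or men"). The sample size section {14} describes the same allocation for the pooled comparison: "Participants will be randomized using a 2:1 allocation ratio (intervention to control"). The primary effectiveness contrast uses that pooling, since {20a} says "both exoskeleton arms (Exo1 and Exo2) will be pooled into a single intervention group and compared to the control group".

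On visibility, the concealment section {16b} accepts that "blinding of participants and intervention personnel is not feasible", and {17a} adds that "neither participants nor those overseeing the intervention will be blinded". On who recruits, {16c} says "Participants are enrolled by trained research staff at the respective study sites".

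The safeguards in {16b} and {16c} are central computer randomisation, release of the assignment only after enrolment and confirmed eligibility, and no staff access to the coming sequence. Varying or withholding the block size is not mentioned. The trial status section says that recruitment began in January 2026 and should end by June 2027.

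**The concern.** Central randomisation hides the list. It does not hide what can be worked out from past assignments when the block size is known and constant. Once two controls have appeared in a block of 6, every remaining place is exoskeleton. Once four exoskeletons have appeared, every remaining place is control. The last place is always known. The strata are small local units, essentially one company split by sex, where it is easy to see who wears a device.

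A recruiter who expected a particular slot could, without any bad intent, hasten, delay or discourage a worker. There is some room for this. The consideration period in {15} has no stated length, and the exclusion for inability or unwillingness to comply (Table 1) involves judgement.

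Two results could be affected. One is the contrast in self-reported complaints (CMDQ), if workers with more or fewer complaints were steered to one arm. The other is wearing compliance in the exoskeleton arms, if keen workers were steered there. The estimates are meant to inform later confirmatory trials, so a distortion would carry forward.

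**Working it through.** **Inputs from the article.** Block size 6 and ratio 1:1:1 ({16a}), so each block has 2 control, 2 model 1 and 2 model 2 places. For the pooled contrast ({20a}) that is 4 exoskeleton (E) and 2 control (C). The target is 120 complete datasets, with at most 240 randomised ({14}). The number of companies is not given; {15} says only that there will be several.

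**The plan's own figure.** The article gives no figure for predictability. Its maximum sample size, used below, reproduces: 120 / (1 − 0.5) = 240, split 160 and 80.

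**Certain allocations in a completed block.** There are C(6,2) = 15 equally likely orders of 4 E and 2 C. A place is certain when only one type remains.

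| Place | Orders in which it is certain | Probability |
|---|---|---|
| 1 | 0 | 0 |
| 2 | 0 | 0 |
| 3 | 1 (both C in the first 2) | 0.067 |
| 4 | 3 (both C in the first 3) | 0.200 |
| 5 | 6 + 1 (both C, or all 4 E, in the first 4) | 0.467 |
| 6 | 15 | 1.000 |

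Sum: (1 + 3 + 7 + 15) / 15 = 26/15 = 1.733 per block. Share: 1.733 / 6 = 28.9%. The exact arm out of three is certain in 20.0% of allocations.

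**Best guess.** The chance of a correct best guess at places 1 to 6 is 0.667, 0.667, 0.667, 0.733, 0.733 and 1.000. The mean is 4.467 / 6 = 74.4%. Always guessing exoskeleton gives 4/6 = 66.7%.

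**Unfinished blocks lower the share.** A stratum that stops at 3, 4 or 5 participants has (1/15)/3 = 2.2%, (4/15)/4 = 6.7% or (11/15)/5 = 14.7% certain.

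**Spread over strata.** This is a simulation over an assumed number of equal strata, with an observer who knows all earlier allocations in the stratum:

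| Assumed strata | 240 randomised | 120 randomised |
|---|---|---|
| 8 | 27.1% | 25.3% |
| 20 | 24.4% | 19.8% |
| 40 | 19.8% | 9.2% |

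**Effect of the remedy.** This is a simulation of an observer who knows which sizes are possible but not where blocks begin or end, for strata of 12 and 24 participants:

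| Block sizes | Certain | Best guess correct |
|---|---|---|
| Fixed 6 | 29% | 74% |
| Random 6 and 9 | about 5% | about 72–73% |
| Random 3, 6 and 9 | about 3% | about 73% |

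**The case against.** The case against is substantial, and much of it stands.

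- **29% is a ceiling.** It needs completed blocks and an observer who misses nothing. With many small strata the share drops, to 9% for 120 participants in 40 strata. This stands, and the figure should be read as a maximum.
- **The route is inferred.** A reader might conclude that enrolling staff know all earlier allocations in their stratum. No section says so. Section {16c} names who enrols, and {17a} says that participants and those overseeing the intervention are unblinded, but the article does not say that these are the same people. It also does not say whether a company's workers are randomised one by one. If all were enrolled before any was assigned, the opportunity would largely disappear. This stands as a limit on the claim. On-site enrolment and a device worn at work still make the route plausible.
- **Other features narrow the opportunity.** Assignment follows confirmed eligibility, invited roles are agreed beforehand with management ({10}), and recruitment runs in waves ({15}). Controls receive the device after 3 months, which weakens the motive to steer keen workers. These points reduce the risk but do not remove it.
- **Retention.** A reader might infer that the retention target is biased too. As defined under the adherence endpoint, retention is one proportion over all participants, so moving people between arms does not bias it directly. This part of the argument is not supported.
- **The remedy gains less than the fall in certain allocations suggests.** Best-guess accuracy falls by only 1 to 3 points, and selection can act through good guesses as well as certain ones. This stands.

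The estimation focus of the effectiveness endpoint is a weaker defence, because a biased estimate misleads the planning of the next trial as much as a biased test would.

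**Conclusion.** The point holds as an avoidable weakness in the randomisation design. A single published block size of 6, in small visible strata of an open-label trial that is still recruiting, leaves up to 28.9% of exoskeleton-versus-control allocations certain to someone who tracks them perfectly through completed blocks. The plausible range is about 20% to 27% at 240 participants and 9% to 25% at 120, on the assumption of 8 to 40 equal strata, because the article does not give the number of companies.

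A reader might go further and infer that concealment has failed or that the results are biased. The article does not support that. The stated safeguards do hide the list, and nothing shows that anyone has inferred or used the sequence. What remains is a risk that the safeguards do not address and that could affect the complaint contrast and the wearing-compliance figures.

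**What to change.** 1. For all blocks not yet opened, set the randomisation software to randomly varying block sizes, for example 6 and 9.
2. In the protocol and registry, state only that block sizes vary at random. Amendments are documented in the registry and sent to the study team ({25}), so wording that named the sizes would defeat the purpose.
3. Keep the actual sizes in a restricted document, away from enrolling staff, until recruitment ends.
4. Report how many participants were randomised under the fixed size.

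The cost is one software setting, one sentence of amendment text and its approval. The statistical price is slightly more arm imbalance from unfinished blocks in small company-by-sex strata, which works somewhat against the balance that {16a} seeks. The gain should be described accurately: most certain allocations disappear, while general guessability changes little. Allocations already made cannot be repaired, so an early change is worth more.

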### Concealment mechanism {16b}

Allocation concealment will be ensured through centralized computer-based randomization. Group assignment is generated by the randomization software only after a participant has been enrolled and baseline eligibility has been confirmed. Investigators involved in recruitment and enrollment will not have access to the upcoming allocation sequence.

Due to the visible and physical nature of the intervention (use of a back-support exoskeleton), blinding of participants and intervention personnel is not feasible.

### Implementation {16c}

The random allocation sequence is generated by a member of the study team who is not involved in participant enrollment or data collection.

Participants are enrolled by trained research staff at the respective study sites.

Group assignment is conducted automatically by the randomization software after enrollment, ensuring allocation concealment.

## Assignment of interventions: blinding

### Who will be blinded {17a}

This study is designed as an open-label randomized controlled trial, as blinding of participants and staff delivering the intervention is not feasible due to the visible and physical nature of the exoskeleton. Consequently, neither participants nor those overseeing the intervention will be blinded. However, to mitigate potential bias, outcome assessors and data analysts will remain blinded to group assignment, and all data will be pseudonymized prior to analysis to ensure objectivity. We acknowledge the risk of performance bias and detection bias, particularly in subjective outcome measures such as perceived workload, fatigue, or job satisfaction. To address these risks, we use validated and standardized questionnaires to reduce the influence of personal interpretation. Furthermore, participants in both arms will receive comparable levels of researcher attention and contact, helping to minimize differential expectations or behavior changes that could otherwise influence the results.

### Procedure for unblinding if needed {17b}

N/A. Since only data analysts and outcome assessors are blinded, unblinding during the trial is generally not required.

## Data collection and management

### Plans for assessment and collection of outcomes {18a}

No formal pre-screening data are collected prior to enrollment. Recruitment is based on voluntary participation within cooperating companies. Interested employees receive detailed study information and are enrolled after providing written informed consent, provided that inclusion criteria are met.

Baseline data collection is initiated after enrollment. Outcome assessments will be conducted on-site at the participating companies and hospitals. Data collection includes sociodemographic characteristics and a brief personal medical history obtained through an open-ended questionnaire administered at baseline.

Outcome parameters are documented in standardized data sheets and entered into a secure database. Table 3 provides a detailed schedule of participation and measurement time points, including the constructs to be assessed and the corresponding validated instruments. All assessments will be conducted and monitored by trained study personnel at predefined time points to ensure the quality, consistency, and comparability of the collected data.

### Plans to promote participant retention and complete follow-up {18b}

No changes are planned for the assigned intervention, as the study aims to evaluate the practical usability of the exoskeleton under real-world working conditions. If participants discontinue the intervention (e.g., due to discomfort), these decisions will be considered meaningful outcomes that provide valuable insights into user acceptance.

To encourage participant engagement and promote data completeness, questionnaires are administered using the online survey platform LimeSurvey [49]. For each assessment, participants receive an email invitation containing a personalized survey link. Participants have a 1-week period to complete each questionnaire. If a questionnaire has not been completed within 5 days, an automated reminder email is sent. Within the questionnaire, most items are mandatory and participants cannot proceed without providing a response, thereby minimizing item-level missing data.

Any study dropouts and instances of non-response at the questionnaire level will be documented. All collected data will be included in the analyses in accordance with the statistical methods described below.

### Data management {19}

The trial management team develops the case report forms (CRFs) and provides them to the participating centers in electronic format (eCRFs) using the LimeSurvey application [49].

Source Data, according to ICH-GCP E6, includes all information from original records and copies of original records of findings, observations, or other activities within the trial that are required for traceability and recording of variables. The original data is contained in the original documents (original records or certified copies), and its origin can be traced through the case file (electronically or in paper form). The data collected will be reviewed by two researchers and organized for statistical evaluation.

### Confidentiality {27}

Information about participants will be collected, communicated, and stored with the highest level of confidentiality during the trial. Each participant will be assigned a unique identification number to ensure their anonymity in all related documents and data. Information will be stored in secure electronic databases protected by passwords, while physical documents will be kept in locked cabinets accessible only to authorized research staff and monitors. All data are collected, stored, and processed by the European data protection regulation.

The data is stored on Magdeburg-Stendal University of Applied Sciences servers. At the end of the trial, the database will be locked (database lock). After that, any changes to the data in the database can only be made with a written agreement signed by both the trial management and the data manager. Personal information about participants will not be revealed in any publications or reports.

### Plans for collection, laboratory evaluation and storage of biological specimens for genetic or molecular analysis in this trial/future use {33}

N/A. No biological specimens were collected as part of this trial.

## Statistical methods

### Statistical methods for primary and secondary outcomes {20a}

Data will be analyzed using IBM SPSS Statistics (Version 29; IBM, Armonk, New York, USA). For the primary effectiveness analysis, both exoskeleton arms (Exo1 and Exo2) will be pooled into a single intervention group and compared to the control group. Exploratory analyses will additionally compare the three randomized arms separately. The primary analysis will follow an intention-to-treat (ITT) approach, meaning that all randomized participants will be analyzed in the groups to which they were initially assigned. Data from participants with missing information will be analyzed under the "missing at random" assumption. Per-protocol analyses will include only those participants in the intervention group who wore the exoskeleton at least 75% of the days each week when lifting tasks are performed. These analyses will be conducted as sensitivity analyses to assess the robustness of effectiveness-related estimates with respect to intervention adherence and wearing behavior. 

The primary applicability endpoint will be assessed descriptively. To evaluate the metric endpoints, mixed-effects models with a repeated measures structure will be estimated using restricted maximum likelihood. In this model, the measured values collected during all study visits will be considered the dependent variable. We will include treatment group (exoskeleton vs. control) and categorical time as fixed effects. Interactions between the group and time (categorical) will also be modeled. For random effects, we will include an intercept for each subject. Within the mixed models, we will estimate 95% confidence intervals (CIs) and *p*-values for contrasts between groups for the 3-month period. For sensitivity analyses, only patients with complete paired baseline and 3-month follow-up data will be included, ensuring a time difference within groups is analyzed using a paired *t*-test for dependent samples.

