##### Co-primary effectiveness-related endpoint

The co-primary effectiveness-related endpoint is the change in musculoskeletal complaints from baseline to 3 months, assessed using the Cornell Musculoskeletal Discomfort Questionnaire (CMDQ) score, comparing the intervention group with the control group.

This endpoint will be analyzed using longitudinal models to estimate mean changes, effect sizes, and 95% confidence intervals. Given the feasibility focus of the trial, these analyses are intended to generate preliminary evidence and inform the design and sample size calculation of future adequately powered confirmatory studies. No formal multiplicity adjustment will be applied, as the trial is not powered for confirmatory testing.

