Sector-specific challenges further influence feasibility and implementation. In the logistics sector, difficulties in recruiting participants for a 3-month intervention period may arise due to high employee turnover, particularly in large companies employing temporary or seasonal workers [55]. In contrast, the healthcare sector presents different challenges related to the highly variable nature of daily work tasks. Physically demanding activities such as patient lifting during mobilization or emergency situations alternate with less physically demanding tasks, including documentation or patient transfers. During these latter activities, the exoskeleton may be perceived as disruptive, raising questions about repeated donning and doffing throughout the workday. In addition, hygiene requirements represent a critical consideration in healthcare settings and must be carefully addressed prior to implementation.

Despite these limitations, to our knowledge, ELSA LogiCare is among the first randomized controlled trials to investigate the medium-term effects of passive back-support exoskeletons under real-world working conditions. If shown to be effective and feasible, exoskeletons could complement existing ergonomic interventions and contribute to the development of evidence-based recommendations and occupational health policies. Furthermore, the findings may inform manufacturers, employers, and policymakers and support the design of future trials that integrate effectiveness evaluation with comprehensive process evaluation approaches.

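### The stated effectiveness model omits the randomisation strata, leaves the arms' baseline means free and does not fix its contrast, which costs precision and exposes the estimate to any dropout that differs by sector and arm

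*Protocol article*

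**What the plan says.** The section on statistical methods for primary and secondary outcomes (20a) sets out the model term by term. On the response: "the measured values collected during all study visits will be considered the dependent variable". On fixed effects: "We will include treatment group (exoskeleton vs. control) and categorical time as fixed effects". On the interaction: "Interactions between the group and time (categorical) will also be modeled". On random effects: "For random effects, we will include an intercept for each subject". Confidence intervals and p-values are then to be given "for contrasts between groups for the 3-month period". The endpoint section defines the quantity of interest as "the change in musculoskeletal complaints from baseline to 3 months".

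The section on sequence generation (16a) reads: "Randomization will be stratified by sector (logistics or healthcare), trial site (participating cooperation partners), and sex (women or men"). None of these three factors is among the model terms. Sector and sex return only as optional exploratory subgroup analyses (20b), and trial site does not return at all.

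Other relevant facts:
- Table 3 schedules the D-CMDQ at baseline and week 12 only.
- The sample size section allows for dropout of up to 50%.
- Missing data are handled as missing at random (20a, 20c).
- The participant timeline (13) places the baseline assessment after random assignment, in an open-label trial.

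**The concern.** The trial is built for estimation. Its effectiveness output is an effect size, its variability and a 95% confidence interval, and these are to feed the sample size of a later confirmatory trial. Three features of the model bear on that output.

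- **Baseline.** Baseline enters as one more response with its own mean in each arm. Randomisation makes the two means equal in expectation, so estimating them separately gives away precision.
- **Strata.** Factors used to balance the arms are left out. Depending on the contrast, the standard error may then not reflect the balance that the design achieved. The missing-data assumption also conditions only on arm and baseline score, not on sector, site or sex.
- **Contrast.** The 3-month wording fits either the group difference at month 3 or the group difference in change. The two have different standard errors and respond differently to the first two features.

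**Working it through.** **Inputs from the article.** 80 and 40 complete datasets; dropout up to 50%; two D-CMDQ time points (Table 3); endpoint defined as change to 3 months.

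**Inputs assumed, because the article gives none.** Baseline-outcome correlation ρ from 0.3 to 0.8; equal variances at the two visits. For the simulations: ρ = 0.6, sector explaining 25% of the outcome variance, no treatment effect, 3,000 replicates. Only sector was simulated as a stratum.

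**Step 1: the plan's own figure.** 120/(1 − 0.5) = 240; 80/0.5 = 160; 40/0.5 = 80. All agree with the sample size section. No SD, effect size or interval width is stated, so nothing further can be reproduced.

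**Step 2: baseline handling, complete data.** In units of the outcome SD, SE = k × √(1/80 + 1/40) = k × 0.1936, where
- k = √(2(1 − ρ)) for the change contrast,
- k = 1 for the unadjusted month-3 contrast,
- k = √(1 − ρ²) for a baseline-adjusted contrast.

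The SE ratio of adjusted to change is √((1 − ρ²)/(2(1 − ρ))) = √((1 + ρ)/2). The ratio of adjusted to month 3 is √(1 − ρ²). Half-widths of the 95% interval (1.96 × SE):

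| ρ | change | month 3 | adjusted | adjusted/change | adjusted/month 3 |
|---|---|---|---|---|---|
| 0.3 | 0.449 | 0.380 | 0.362 | 0.81 | 0.95 |
| 0.5 | 0.380 | 0.380 | 0.329 | 0.87 | 0.87 |
| 0.6 | 0.339 | 0.380 | 0.304 | 0.89 | 0.80 |
| 0.7 | 0.294 | 0.380 | 0.271 | 0.92 | 0.71 |
| 0.8 | 0.240 | 0.380 | 0.228 | 0.95 | 0.60 |

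The adjusted contrast is more precise at every ρ tried. At ρ = 0.6 the planned interval is 12% wider (change) or 25% wider (month 3) than the adjusted one.

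**Step 3: strata, complete data (120 participants).**
- Change contrast: SE 0.173 with or without sector. An additive sector effect cancels within each subject.
- Month-3 contrast: model SE 0.194 without sector, against an actual spread of 0.171, so coverage is 97.3%. With sector, the SE is 0.167.
- Common baseline mean: SE 0.154 alone, 0.148 with sector and sector × time.

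**Step 4: dropout (240 randomised, about half lost).** Bias of the change contrast, in SD:

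| Dropout depends on | model as stated | plus sector | plus sector × time |
|---|---|---|---|
| baseline × arm | +0.002 | +0.006 | +0.006 |
| sector × arm (retention 70%/30%), additive sector effect | +0.170 (coverage 83%) | +0.006 | +0.004 |
| the same, and sectors differ by 0.5 SD in change | +0.360 (coverage 44%) | +0.174 | −0.001 |

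A common baseline mean without the strata does not help in the last two rows (bias 0.168 and 0.361). Baseline handling and strata are therefore separate issues: the first concerns precision, the second protection against selective dropout. The 70%/30% pattern is deliberately strong.

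**The case against.** Several points on the other side are good ones.

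- **The article condenses a fuller plan.** Covariates are often left to an SAP, and the text does not say that these are the only terms. However, it gives fixed effects, interaction and random effects one by one, so a reader would take it as the model. This is a model as stated, not a detail passed over.
- **A reader might infer that baseline is ignored and that this weakens the missing-at-random assumption.** The documents do not support that. Baseline values are part of the response, so the likelihood already conditions on them; step 4 shows no material bias when dropout depends on baseline and arm.
- **A reader might infer that leaving out the strata widens the interval whatever the contrast.** For change, which is the defined endpoint, it does not do so if strata effects are additive.
- **A reader might infer that the plan predicts dropout by sector.** The Discussion says that, in logistics, problems "may arise due to high employee turnover, particularly in large companies employing temporary or seasonal workers", but the problems named there are difficulties in recruiting, and the statement is hedged. Moreover, dropout that depends on sector equally in both arms cancels from the group contrast unless the treatment effect itself differs by sector. Bias needs dropout that differs by sector and arm together. The Discussion's remark that healthcare staff may find the device disruptive makes this plausible, since only device users are affected, but nothing states it.
- **The remedy for baseline has a condition.** With baseline assessed after a known allocation, a self-reported score may already differ between arms. A common baseline mean or a baseline covariate would then rest on doubtful ground. This objection stands in full and shapes the fix.
- **The trial is not powered for confirmatory testing.** True, but this makes interval width and bias more central to what it delivers, not less.

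**Conclusion.** The point holds within limits. The stated model leaves out the three randomisation factors, leaves the baseline means free and does not fix its contrast.

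- **Precision lost through baseline.** For an assumed ρ of 0.3 to 0.7, adjustment would narrow the interval by 19% to 8% against the change contrast, or by 5% to 29% against an unadjusted month-3 contrast.
- **Strata and interval width.** Omission makes the month-3 interval too wide. It leaves the change interval as it is under additive effects.
- **Strata and bias.** Bias arises only if dropout differs by sector and arm together. Under the strong assumed patterns it was 0.17 to 0.36 SD; these figures illustrate the exposure and do not forecast it. The exposure is real because up to half the participants may be lost and Table 3 provides no D-CMDQ between baseline and week 12. The intervention description (11a) does list musculoskeletal complaints among the 4-weekly assessments; if the D-CMDQ were in fact collected then, the model would have more to condition on.

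The analysis is not invalid as planned. It is less precise than it could be and less well protected against selective dropout, and both can be mended now.

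**What to change.** 1. Add sector and sex, each with its interaction with time, as fixed effects, and trial site as a random intercept. Group sites if partners are small.
2. Name one contrast at 3 months as the effectiveness estimate, consistent with the endpoint definition.
3. Have the D-CMDQ at baseline completed before allocation is disclosed, and amend the participant timeline accordingly. Recruitment began in January 2026, so record which order was followed for those already enrolled.
4. With that order in place, either constrain the arms to a common baseline mean or use baseline as a covariate with the post-baseline value as the response.

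The cost is small: a few more model parameters, a fixed order of steps at the baseline visit, and a change of wording. Sector, site and sex are already known at randomisation, and the baseline score is already collected. Under the assumptions of step 3, the SE with sector and a common baseline mean falls to 0.148, from 0.173 (change) or 0.194 (month 3).
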